### Data Sources

The study will be carried out using secondary data previously collected from various health databases at the population level. The researchers accessed the data set through the PADRIS program (Programa públic d’analítica de dades per a la recerca i la innovació en salut a Catalunya) of AQuAS (L'Agència de Qualitat i Avaluació Sanitàries de Catalunya) [13]. This program is designed to facilitate research by reusing data from the Catalan Public Utilization System (Sistema Sanitari Integral d’Utilització Pública de Catalunya [SISCAT]) with maximum ethical and data protection guarantees. The data will be pseudonymized and subjected to a study of the risk of reidentification of individuals from the data set, thus minimizing this risk before being used by the researchers.

The general characteristics of the original databases from which the study data will be obtained are summarized below:

Hospital CMBD is a database in which diagnoses and procedures performed on hospitalized patients are recorded throughout the Spanish territory; all public hospitals and the majority of private hospitals (>95% hospital coverage) are included [14].Estació Clínica d'Atenció Primària (ECAP) is an electronic medical history program launched in 2001 and used by family doctors, pediatricians, and nurses from the Catalan Institute of Health (Institut Català de la Salut [ICS]) primary care centers when they visit patients; it includes all previous illnesses known to the primary care physician and records of the health care process in the outpatient setting, including assessments by health care personnel, diagnostic tests, and treatment, among others. The PADRIS program has only provided data since 2006, after which data are considered to be of good quality.The registry of causes of death is prepared by the INE using data from the Medical Certificate of Death or Statistical Bulletin of Death, Statistical Bulletin of Judicial Death, and Statistical Bulletin of Childbirth. It is prepared following the criteria established by the WHO (World Health Organization) in the International Classification of Diseases (ICD), which includes more than 12,000 diseases.Electronic prescription has been implemented in Catalonia progressively since 2010 and is currently deployed in 100% of primary care centers, pharmacies, and public hospitals in Catalonia. Prescribing and dispensing data will be obtained from the Comprehensive Health Information System of the Catalan Health Service (Servei Català de la Salut [CatSalut]), which is a computerized system used by the doctors of the national health system in Catalonia to prescribe financed pharmacological treatments to their patients and the pharmacies to dispense them; it contains information on the date of the prescription, the active ingredient, and dose, among other variables. Unfunded treatments can be prescribed using this tool but are often prescribed by other means (paper prescriptions).

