### Duration

The patients in cohort 1 will have been diagnosed with the cancer under study between 2006 and 2012, both inclusive, and their survival will be retrospectively monitored for 5 years after diagnosis or until death if it occurs earlier. Cohort 2 will include patients without cancer who have had any type of contact with the health care system between 2006 and 2012, and these individuals will be followed up retrospectively for 5 years or until death if it occurs earlier.

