### Outcome Variables and Measurements

The primary end point is survival, calculated from the date of entry in the database until death or until 5 years of follow-up are reached. For patients in cohort 1, the earliest date of cancer diagnosis for which they have been selected to be part of the cohort will be considered the date of entry into the study (inclusion criterion).

As study variables, the following data will be collected from all patients:

List of diagnosed diseases (data source: CMBD and ICS ECAP diagnostic registry)Date of death (data source: INE cause of death registry)Cause of death (data source: INE cause of death registry)Pharmacological treatment (data source: Catalan electronic prescription), including all prescribed active ingredients, drug withdrawal dates from pharmacies, consumed doses, and prescribed regimen, during the entire follow-up periodSex (data source: Sistema Integral d'Informació de Salut)Date of birth (data source: Sistema Integral d'Informació de Salut)Basic health area (data source: Sistema Integral d'Informació de Salut)

For the patients included in the study with one of the cancers under study (cohort 1), the following variables will also be collected:

Type of cancer and presence of metastases (data source: CMBD and ICS ECAP diagnostic registry)Date of diagnosis for which the patient is included in the cohort (data source: CMBD and ICS ECAP diagnosis registry)Surgical treatment of the cancer (data source: CMBD)Date of surgical treatment (data source: CMBD)

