### Data Curation

The data used in this study will be obtained from different databases, which must be merged for the analysis. None of the databases will be sorted by patient but by other types of entries (drugs, diagnoses, procedures performed, etc); therefore, the same patient could appear multiple times in each of them. Thus, first, a date will be associated with each event, and the information in the databases will be sorted by patient, with each patient as an entry that appears only once.

The coding of diseases and therapeutic procedures has undergone changes during the years of collection in the cohort, transitioning from using International Classification of Diseases, Ninth Revision (ICD-9) coding to ICD-10 coding. Consequently, all the data with ICD-9 coding will have to be converted to ICD-10 using the conversion tables provided by the Government of Catalonia (Generalitat de Catalunya) on their website [15].

In the pharmacological dispensing database, the active principles will be collected through the Anatomical Therapeutic Chemical (ATC) Classification System, and the amount dispensed monthly will be determined using the number of defined daily doses (DDDs) [16]. DDDs change over the years and are not uniform for different active ingredients or for drugs that form different groups as defined by the ATC4 codes. Thus, when necessary, DDDs will be transformed into units of mass for each of the drugs using the tables provided by the WHO with the evolution of DDDs over time [17].

One of the databases managed includes patients with metastases of any origin. For these patients, their previous diagnoses will be traced, and all the codes for both the CMBD and the ECAP will be analyzed to search for cancer diagnoses before metastasis to determine the origin of the cancer.

Finally, a patient rejection process will be applied based on the consistency of dates between the different databases. Following this principle, all those patients who, having been included in the database, do not have electronic prescription records will be rejected. In addition, all patients without registration or enumeration in the death databases will be excluded. Finally, patients with inconsistent dates will be excluded, for example, with postdeath records in the CMBD, ECAP, or electronic prescription.

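### Supplied data and cohort entry both start in 2006 with no stated cancer-free look-back, so some cancers diagnosed earlier can enter as new, and the resulting bias need not run only toward the null

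*Protocol article*

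**What the plan says.** Under Data Sources, the item on the primary care record (ECAP) states: "The PADRIS program has only provided data since 2006, after which data are considered to be of good quality". The same section says that the whole data set is obtained through PADRIS. Under Duration, cohort 1 consists of patients "diagnosed with the cancer under study between 2006 and 2012, both inclusive". Under Outcome Variables and Measurements, the date of entry is "the earliest date of cancer diagnosis for which they have been selected to be part of the cohort", and the primary end point is "survival, calculated from the date of entry in the database until death or until 5 years of follow-up are reached".

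The two diagnostic sources differ. The hospital database (CMBD) is one where "diagnoses and procedures performed on hospitalized patients are recorded throughout the Spanish territory". ECAP was launched in 2001, and of it the article says that "it includes all previous illnesses known to the primary care physician".

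Data Curation looks back at earlier diagnoses only for patients with metastases, to "search for cancer diagnoses before metastasis to determine the origin of the cancer". Its exclusions concern missing prescription records, missing death-registry records and inconsistent dates. The section on potential sources of bias treats reverse causality, immortal time and medical surveillance. The Discussion accepts that registration follows diagnosis. It concludes that this places some long survivors in the comparison group and so pulls results toward the null.

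**The concern.** A 2006 entrant has little or no observed time before entry, and no rule requires any. The hospital database records admissions, so a readmission in 2006 for a cancer found in 2004 also yields a qualifying code. If the 2004 date is not in the extract, the patient looks newly diagnosed.

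Two things follow. First, time zero is wrong. The safeguard against immortal time counts drugs taken up to a landmark, with month 3 after diagnosis as its example. For a patient diagnosed two years before the first code, that window actually closes at month 27. Second, the patient has survived from diagnosis to first code. In cancers where deaths cluster early, those who remain have better further survival than new patients.

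The main comparison sets drug use in 5-year survivors against drug use in those who died. If prevalent patients are over-represented among survivors and use different drugs because they are in a later phase of disease, some of the difference could reflect phase of disease and not the drug. That can act away from the null, a direction the Discussion does not consider.

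**Working it through.** The documents give no count of prevalent cases, so there is no plan figure on this point to reproduce. The calculation below is an illustration for lung cancer.

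**Inputs from the article.** Table 2 gives 4,079 new lung cases a year and 18.1% alive at 5 years. As a check, 4,079 × 0.181 = 738, the printed number. Entry years 2006 to 2012 make seven, so new cases are 7 × 4,079 = 28,553 and their 5-year survivors 28,553 × 0.181 = 5,168.

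**Assumptions, not in the documents.** Incidence before 2006 equals Table 2. The prevalent pool is everyone diagnosed in the five years before 1 January 2006 and still alive. A share f of 5% to 25% of that pool is first coded in 2006. Survival is S(t) = exp(−λt^k), fixed so that S(5) = 0.181.

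**Falling hazard, k = 0.6.**
- λ = −ln(0.181) / 5^0.6 = 1.709 / 2.627 = 0.651.
- Pool = 4,079 × ∫S(a)da over 0 to 5 = 4,079 × 1.894 = 7,726.
- Pool members alive five years later = 4,079 × ∫S(a+5)da over 0 to 5 = 4,079 × 0.5895 = 2,404.
- Further 5-year survival = 2,404 / 7,726 = 31.1%, against 18.1% for new cases.

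| | f = 5% | f = 25% |
|---|---|---|
| Prevalent entrants (f × 7,726) | 386 | 1,932 |
| of whom alive at 5 years (f × 2,404) | 120 | 601 |
| Share of 2006 lung entrants | 386/(386+4,079) = 8.7% | 1,932/(1,932+4,079) = 32.1% |
| Share of seven-year lung cohort | 386/(386+28,553) = 1.3% | 1,932/(1,932+28,553) = 6.3% |
| Share of 5-year survivors, 2006 entrants | 120/(120+738) = 14.0% | 601/(601+738) = 44.9% |
| Share of 5-year survivors, seven years | 120/(120+5,168) = 2.3% | 601/(601+5,168) = 10.4% |
| Apparent 5-year survival, seven years | (120+5,168)/(386+28,553) = 18.3% | (601+5,168)/(1,932+28,553) = 18.9% |

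**Constant hazard, k = 1.** λ = 1.709 / 5 = 0.342, and the pool is larger: 4,079 × (1 − 0.181) / 0.342, or 9,772 with λ unrounded. Its further 5-year survival is exactly 18.1%, so the prevalent share is the same among survivors as in the cohort and 5-year survival does not move. Only the misplaced time zero and landmark remain.

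**The case against.** The strongest reply is that the criterion as written already requires a diagnosis in 2006 to 2012, and that the date of diagnosis is a collected variable. A cancer known to date from 2004 fails that test. ECAP dates from 2001 and holds earlier illnesses, so the supplied records may carry earlier onset dates. The 2006 sentence stands in the ECAP item, and nothing separate is said about the hospital database. This stands, and it narrows the point to old cancers whose original date is not in the extract. It does not remove it: the article never says that earlier dates were supplied or used to exclude prevalent cases, and ECAP as described covers the primary care centers of one provider, so it may not cover every patient known only from hospital records.

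A second reply is that a condensed article may omit a washout rule. That is fair for operational detail. But the article itself fixes the window, the time zero and the exclusions, and draws a conclusion on the direction of bias that does not follow from them.

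Several stronger readings are tempting and not supported. A reader might combine the larger pool of 9,772 with a markedly better further survival. Those belong to different models: the larger pool needs a constant hazard, under which there is no survival enrichment. A reader might also infer that drugs used by stable survivors will appear protective. That would need a difference in drug use that remains after the planned matching and adjustment, and no figure in the article shows one. Nor is the Discussion simply wrong: anyone alive five years after registration did live at least five years from diagnosis, and this holds for prevalent patients too.

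Finally, electronic prescribing was phased in from 2010 and patients without such records are rejected. That is a separate selection on survival, which a later start of entry in 2007 would not cure.

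**Conclusion.** The point holds in a limited form. Because data and entry begin together and no look-back is stated, some cancers diagnosed before 2006 can enter as new, with time zero and the exposure landmark too late. Any effect is concentrated in 2006 and diluted over seven years. In the lung illustration, prevalent cases are about 9% to 32% of 2006 entrants, but only 1.3% to 6.3% of the whole lung cohort and 2.3% to 10.4% of its 5-year survivors.

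These figures rest on the assumed first-coded share, a five-year pool, constant incidence and a Weibull shape of 0.6. None comes from the documents, and with a constant hazard the effect on 5-year survival is nil. No bias in an odds ratio or hazard ratio has been shown. What can be said is that bias away from the null is possible, so the Discussion's account of late registration is incomplete. The safeguard is cheap enough that it should be adopted.

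**What to change.** 1. Exclude patients whose ECAP or CMBD records carry a date before 2006 for the listed cancer, and say whether such dates were supplied.
2. Keep the earliest date as time zero, and require at least 12 months of data before entry with no listed code for the same cancer. In practice 2006 becomes a washout year and entry opens on 1 January 2007.
3. Add the 2006 entrants back as a sensitivity analysis.
4. Amend the Discussion to say that a patient registered late must have survived until registration, so the direction of bias is not only toward the null.

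The work is one inclusion sentence, one filter and one rerun. The price is up to about one seventh of the cohort in the main analysis: 102,860 / 7 ≈ 14,700 patients if entries are evenly spread, which the article does not state. The remedy is partial, because an old cancer that is not coded in 2006 can still enter in a later year.

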### Outcome Variables and Measurements

The primary end point is survival, calculated from the date of entry in the database until death or until 5 years of follow-up are reached. For patients in cohort 1, the earliest date of cancer diagnosis for which they have been selected to be part of the cohort will be considered the date of entry into the study (inclusion criterion).

As study variables, the following data will be collected from all patients:

List of diagnosed diseases (data source: CMBD and ICS ECAP diagnostic registry)Date of death (data source: INE cause of death registry)Cause of death (data source: INE cause of death registry)Pharmacological treatment (data source: Catalan electronic prescription), including all prescribed active ingredients, drug withdrawal dates from pharmacies, consumed doses, and prescribed regimen, during the entire follow-up periodSex (data source: Sistema Integral d'Informació de Salut)Date of birth (data source: Sistema Integral d'Informació de Salut)Basic health area (data source: Sistema Integral d'Informació de Salut)

For the patients included in the study with one of the cancers under study (cohort 1), the following variables will also be collected:

Type of cancer and presence of metastases (data source: CMBD and ICS ECAP diagnostic registry)Date of diagnosis for which the patient is included in the cohort (data source: CMBD and ICS ECAP diagnosis registry)Surgical treatment of the cancer (data source: CMBD)Date of surgical treatment (data source: CMBD)

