### Participants and Settings

The study population will be patients with the following cancers whose estimated survival at 5 years is less than 20%: lung, pancreas, esophagus, gastric carcinomas, hepatocarcinoma, and metastatic cancers.

Cohort 1 will include all patients registered in the databases of the public health system in Catalonia (Spain) who were diagnosed with any of the diseases under study between 2006 and 2012 (Textbox 1 contains the list of International Classification of Diseases, Tenth Revision [ICD-10] codes) and who have complete data regarding the study variables (see “Outcome Measurements and Variables” section).

Diagnostic codes (International Classification of Diseases, Tenth Revision [ICD-10]) for the pathologies under study.

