**Neoplasm gastric**
C16, C16.0, C16.4, C16.3, C16.1, C16.2, C16.5, C16.6, C16.8, and C16.9

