### Methods to Address Potential Sources of Bias

This study, given its retrospective nature, is potentially affected by a series of biases, whose prevention or compensation will be attempted through various techniques. The 3 most important biases are discussed below:

Reverse causality bias: drugs that are prescribed to patients near death to control their symptoms will appear associated with an increased risk of death in the analyses, with the prescription of these drugs not being the cause of death but a consequence of proximity to death. This bias will be alleviated by eliminating the drugs prescribed 3 months before death from the analysis.“Immortal patient” bias: the longer a patient survives, the more likely he or she is to be diagnosed with pathologies and to consume drugs. This can give the false appearance that the drugs consumed throughout life are the cause of prolonged survival. To control this effect, the analyses only considered the drugs consumed up to a certain date in the group of patients who survived until that same date. For example, in the group of patients who have survived at least 3 months after the diagnosis of their cancer, only drugs consumed at any time up to month 3 after the cancer diagnosis will be considered. Thus, the consumption of the drug will not be explained by longer survival because the entire group will have survived until the moment when the drugs under study are consumed. Patients who consume the study drugs after the established time cutoff point will be eliminated from the analysis. As a comparison group, only patients who have not consumed the drug at any point in their disease evolution will be taken into account.Diagnostic anticipation or “medical surveillance” bias: this bias occurs when patients are included in studies who are in a screening program for cancer because, in such programs, the cancer is diagnosed earlier, which causes the erroneous impression that the individuals live longer. In our database, patients with certain diseases may have undergone frequent diagnostic tests, thus triggering early cancer detection. For example, patients with chronic obstructive pulmonary disease (COPD) may have undergone periodic radiographs, in which lung cancer has been detected early. This may give the impression that COPD, or the drugs used by patients with COPD, are associated with increased survival from lung cancer. To control this bias, patients with a previous pathology that produces greater medical surveillance of the organ where the cancer developed will be eliminated from the analysis.

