
### Sample Size Considerations

Based on a maximum 5-year survival probability of 20% (P=.2, *Q*=.8) and with a significance level of 5% (95% CI) and a power of 80%, it will be possible to detect a difference of 10% between 2 groups with 294 individuals per group. Table 2 shows an initial estimate of the number of survivors at 5 years available during the study period. According to preliminary data not shown, the database available for the study includes a total of 102,860 patients diagnosed with the cancers under study.

**Table 2 table2:** Incidence and estimated survival for the main pathologies under study.

Cancer	New cases each year, n	Estimated 5-year survival, n (%)	Cumulative survivors throughout the study, n
Lung	4079	738 (18.1)	3691
Metastatic colon	6128	852 (13.9)	4259
Metastatic bladder	2444	122 (5)	611
Metastatic kidney	1094	131 (12)	656
Metastatic melanoma	860	171 (19.9)	856
Pancreas	1168	96 (8.2)	479
Esophagus	616	116 (18.8)	579
Metastatic stomach	1089	57 (5.2)	283
Liver	670	118 (17.6)	590

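### Time zero is not fixed for patients with both a qualifying primary code and a later metastasis code; if they are analysed as metastatic, the wait until metastasis can count as guaranteed survival

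*Protocol article*

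**What the plan says.** Under Participants and Settings, the diseases under study are "lung, pancreas, esophagus, gastric carcinomas, hepatocarcinoma, and metastatic cancers". Textbox 1 lists the stomach codes as "C16, C16.0, C16.4, C16.3, C16.1, C16.2, C16.5, C16.6, C16.8, and C16.9", with no stage condition. The lung, pancreas, liver and esophagus codes likewise carry none. C78, C79 and C80.0 form a separate qualifying list.

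Outcome Variables and Measurements runs the primary endpoint, survival, from database entry to death, with follow-up ending at 5 years. Entry of a cancer patient is dated at "the earliest date of cancer diagnosis for which they have been selected to be part of the cohort". The cohort 1 variables listed there include whether metastases are present and one inclusion diagnosis date. No separate metastasis date is listed.

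Data Curation reduces the data to one entry per patient. It adds: "One of the databases managed includes patients with metastases of any origin". For those patients, previous cancer codes are traced to find the origin. The section does not say whether this tracing changes the entry date.

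In Methods to Address Potential Sources of Bias, the landmark is counted from the cancer diagnosis, with month 3 as the example. It continues: "Patients who consume the study drugs after the established time cutoff point will be eliminated from the analysis".

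In Table 2 (Sample Size Considerations) the stomach row is "Metastatic stomach", with 5.2% 5-year survival. The Discussion also refers to stomach cancer as metastatic when it gives classification specificity.

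**The concern.** A patient coded C16 in 2008 and C78.7 in 2010 meets the inclusion criterion twice. If the earliest qualifying date is taken literally, entry is in 2008. If the same patient is then analysed as metastatic stomach cancer, group membership depends on an event in 2010 while survival is counted from 2008. The patient had to live those two years to be in the group. That is the immortal-time problem the plan sets out to control.

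Three consequences follow for a group built this way:

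- Long survivors would be enriched with patients whose metastasis came late. Drug associations would partly reflect time to metastasis, not survival with metastatic disease.
- The landmark would not repair this, because it is anchored on the same date. With a month-3 cutoff, the exposure window would close before metastatic disease existed. A patient who first took a drug at metastasis would be removed from that drug's analysis as a late user.
- The Discussion argues that dating error runs one way only, so that everyone classed as a long survivor truly is one. That would fail here, because a patient could reach 5 years from C16 after living much less than 5 years with metastasis.

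**Working it through.** **Which date each kind of patient receives under the written rule**

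- Colon, bladder, kidney or melanoma origin: the primary code is not in Textbox 1, so only the metastasis code qualifies. Entry is the metastasis date and there is no immortal interval.
- Stomach, metastatic at diagnosis: both codes fall together. Entry is the same on either reading.
- Stomach, C16 first and C78-C80 later, both usable for inclusion: two qualifying diagnoses. Entry is the C16 date if the earliest qualifying diagnosis counts, and the metastasis date if the patient is regarded as selected for metastasis. The text does not say which.
- Lung, pancreas, liver or esophagus with a later metastasis code: the same two-code situation, but Table 2 does not label these groups metastatic. Timing an all-stage group from the primary creates no immortal interval.

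**The plan's own stomach figure**

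Table 2 gives 1089 cases a year and 5.2% survival: 1089 × 0.052 = 56.6 survivors a year, and 56.6 × 5 = 283. Both table entries (57 and 283) are reproduced. This confirms the 5.2% used below but does not test the time-zero rule.

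**Size of the effect, as an illustration**

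Assumptions not given in the documents: 5.2% is 5-year survival measured from metastasis, the hazard after metastasis is constant, all later-metastasising patients have the same lag L in years from primary to metastasis, and they make up a share f of the group.

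Constant hazard: h = −ln(0.052)/5.

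A patient whose clock starts L years before metastasis has to survive only 5 − L years with metastasis to count as a long survivor:

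S(L) = exp(−h(5 − L)) = 0.052^((5 − L)/5)

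- L = 0.5: 0.052^0.9 = 0.070
- L = 1: 0.052^0.8 = 0.094
- L = 2: 0.052^0.6 = 0.170

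For the whole group: (1 − f) × 0.052 + f × S(L).

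| Lag L | f = 1 | f = 0.5 |
|---|---|---|
| 0 | 5.2% | 5.2% |
| 0.5 year | 7.0% | 6.1% |
| 1 year | 9.4% | 7.3% |
| 2 years | 17.0% | 11.1% |

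Example for f = 0.5 and L = 1: 0.5 × 0.052 + 0.5 × 0.0939 = 0.073.

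**The case against.** The best counter-argument is that the entry rule refers to the diagnosis for which the patient was selected. It can therefore mean the earliest record of that one diagnosis across the hospital and primary care databases, which the Discussion says complement each other because of late registration. A patient selected for metastasis would then start at metastasis. Data Curation fits this reading, since earlier cancers are traced to find the origin and not to re-date entry. Stomach may also simply be analysed as all gastric carcinoma from diagnosis, in which case starting at C16 is coherent. The metastatic label appears only in an initial estimate table and in a Discussion example. The article also leaves substudy methods to later papers.

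Much of this stands. A reader might infer that the plan definitely times metastatic patients from their primary, or that metastatic groups in general are affected. The documents support neither: the sentence has two readings, and stomach is the only primary-qualifying cancer in Table 2 labelled metastatic. A reader might also extend the formula to a 3-year lag, get 0.052^0.4 = 30.6%, and say that this breaches the plan's 20% limit. That needs a 3-year lag in every patient. The 20% is also a criterion for choosing cancers from available statistics, not a cap on observed survival. Month 3 is only an example cutoff.

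The objection does not close the gap. For a patient with two selecting diagnoses, the alternative reading still does not say which one counts. An all-stage stomach analysis would not match the label in Table 2 and the Discussion. Time zero of the primary endpoint is something this article sets out to define, so it is not a detail left to another document.

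**Conclusion.** The point holds in a limited form. The entry rule is ambiguous for patients with a qualifying primary code and a later metastasis code, and the stomach group is defined inconsistently. On one of the two readings, and only if these patients are analysed as a metastatic group, the time from primary to metastasis is immortal time and the landmark does not remove it.

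Under the illustrative assumptions, a true 5.2% would appear as 7.3% to 9.4% with a 1-year lag and 11.1% to 17.0% with a 2-year lag, for half to all cases metastasising later. It would not change for patients metastatic at diagnosis. The real size cannot be derived, because the lag and the share are not in the document. Of the nine Table 2 rows, only the stomach row is exposed on its stated label. It does not follow that metastatic results as a whole are invalid. The correction is still worth making before analysis, because it is specific and prevents a bias the plan itself names.

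**What to change.** In Outcome Variables and Measurements, state time zero by type of group:

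- In any group defined by metastasis, survival, the landmark and the exposure windows all start at the first C78-C80 code.
- In an analysis of a primary cancer at all stages, time zero is the primary diagnosis. Metastatic status is fixed from codes dated up to the landmark, or treated as time-varying. Later metastasis codes do not move a patient into a metastatic group.

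Add the date of first metastasis to the cohort 1 variable list. Use one definition of the stomach group in Participants and Settings, Textbox 1, Table 2 and the Discussion.

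The cost is modest. Data Curation already attaches a date to each event, so this is recoding and needs no new data. Some patients will contribute to two separate analyses with different time zeros, which should be stated when those results are reported.
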